### Threats to validity

The main potential threats to the internal validity of the study, including contamination, spill-over effects and Hawthorne-like effects were examined for each of the outcome indicators. From Table 3 it seems that most threats could be avoided by:i.Assigning treatments to districts rather than to communities within districts in order to avoid contamination effects;ii.Avoid informing teachers and households of the control communities that the programme will be implemented after 3 years in order to avoid expectancy effects;iii.Adopt strategies in conducting cognitive and achievement tests that prevent teachers and children from over-performing.

**Table 3 Tab3:** Threats to internal validity (source: adapted from [12])

Indicator	Metric	Spill-over and contamination	Hawthorne and placebo effects
Schooling	Enrolment, attendance, drop-out and completion	Children may attend school from neighbouring communities to have access to meals	Expectation of coming programme in control communities
Cognitive ability	Raven’s matrices, digit span and/or other tests	Very unlikely	Teachers’ and children’s attempt to over-perform in both project and control communities
Attention	Digit span and/or other test	Very unlikely	Teachers’ and children’s attempt to over-perform in both project and control communities
Learning achievement	Scores on language and maths tests	Very unlikely	Teachers’ and children’s attempt to over-perform in both project and control communities
Physical growth	Anthropometric measures of height and weight	Children from other communities may access school meals	Very unlikely
Physical activity levels (PAL)	Parents’ perceptions	Very unlikely	Very unlikely
Diet diversity	Household consumption	Very unlikely	Very unlikely
Micronutrient intake	Iron status, anaemia	Children from other communities may access school meals	Very unlikely
Income	Farm profits	Unlikely, if food purchases are made in control communities	Very unlikely

Given the panel structure of the data there is a potential risk of differential attrition. However, it is difficult to predict why households or farmers from the control groups should respond to the interviews in different ways. Refusal to take part in the interview by households not benefiting from the project seems to be the main threat. However, as shown in Table 3, the project has limited impact on households’ expectations in both project and control groups and, therefore, should have limited impact on response rates.

### Study area and site selection

Selection of the target areas involved three key steps: 1) the first step involved selecting 58 districts at random within Ghana from a sample frame including all districts in the country. The sample frame was stratified by region, and district inclusion was prioritised using data from the GSFP retargeting exercise including data on the prevalence of poverty and food insecurity; 2) the second step involved identifying 2 comparable schools within each of the 58 selected districts. A list was obtained through the GSFP secretariat including schools not currently covered by the GSFP in each district. Data from the annual school census from 2011 to 2012 were then used to match schools not receiving the GSFP and identify ‘best matched’ pair. The allocation of school feeding and control was then randomised (lottery style) within each pair; 3) the third step in the site selection protocol involved the random allocation of districts to the HGSF+/GSFP groups by modelling pilot selection using a set of community- and district-level variables and selecting the permutation of allocation that minimises the *R*^*2*^ for the predicted selection [13].

### Survey instruments

The impact evaluation includes child-, household-, school-, caterer- and community-level data collection as shown in Table 4.

**Table 4 Tab4:** Survey instruments

Instrument	Topic/Modules
Household questionnaire	• Household roster (main demographic characteristics, including of children residing elsewhere) • Education (school enrolment, attendance, education of all household members, time spent in class and working, distance and transport to school, meals while in school, parents’ aspirations, PTA membership and involvement) • Household assets and farm assets (household facilities and durables including land and livestock holdings) • Economic activities (simple income questionnaire on time spent working by household members in wage work, own business and own farm) • Expenditure (monetary expenditure and own production of food, education, health, durables, and non-food expenditure) • Anthropometry (height and weight of parents and children above 6 months of age - parents measurements are taken to assess the genetic potential) • Micronutrient status (haemoglobin levels, anaemia prevalence) • Cognitive and literacy and maths achievement tests (test scores on maths, literacy, Raven’s matrices and digit span test) • Farm income (agricultural production and revenues, input expenditure and depreciation of farm assets) • Other income (a simplified income questionnaire for other income sources like microenterprises, transfers, remittances, gifts, etc.)
School questionnaire	• School facilities (school characteristics including boards, toilets, furniture, books and all school-feeding related characteristics - kitchen, storage room, etc.) • School participation (school-level data on enrolment, attendance and drop-out) • School management and food procurement • Teachers (qualifications, living conditions and aspirations) • Training and monitoring activities

*PTA* Parent-teacher Association

### Methods of analysis

The randomised design allows for the identification of causal impacts of interventions using comparisons of mean outcomes between the randomised treatment arms at endline. The analysis will follow the intention-to-treat approach as protocol and as treated, using econometric analysis for all the relevant outcomes of the intervention. Following Bruhn and McKenzie, impact will be assessed for the different treatment arms using both a ‘difference-in-difference’ (DID) estimator and a single difference analysis of covariance (ANCOVA) model [14].

The DID estimate is calculated as the average change in the outcome of interest (*Y*) in the treatment arm (*T*) minus the change in outcome in the control group (*C*), or:$$ {\Delta}^{DID}=E\left[\left({\overline{Y}}_1^T-{\overline{Y}}_0^T\right)-\left({\overline{Y}}_1^C-{\overline{Y}}_0^C\right)\right]. $$

A difficulty of DID analysis is serial correlation [15] resulting from unobserved factors affecting the outcomes that are themselves correlated over time and that produce auto-correlated errors and invalid standard errors. Serial correlation affects estimated standard errors and can lead to erroneous acceptance or rejection of null hypotheses but not the estimation of the effect size of the intervention. Thus, it may lead to erroneously finding or not finding a statistically significant impact of the intervention. Angrist and Pischke illustrate how this problem can be addressed by calculating clustered standard errors [16], a procedure that is easily implemented using Stata software. Clustered standard errors will also be employed in all cases in which correlated outcomes are observed within the same unit of analysis. For example, when the impact of the intervention is analysed at the school level and test scores within school are obviously correlated. Similarly, clustered standard error will be used at the household level when the project is affecting more than one child within the same family, as in the case of impact on younger siblings.

The single difference model specification has the following form:$$ {Y}_{i1}={\beta}_0+{\beta}_1{T}_i+{\beta}_2{Y}_{i0}+{\varepsilon}_i, $$

where *Y*_*i*0_ is the outcome variable at baseline, *Y*_*i*1_ is the outcome variable at endline and *T*_*i*_ is a dummy variable for the treatment. The ANCOVA estimator has been shown to provide a more efficient estimate of programme impact when auto-correlation of outcomes is low [14].

As additional robustness checks, depending on the level of clustering of the outcome under analysis, we will employ multi-level regression models that account for the hierarchical nature of the data [17]. Multi-level models, also known as mixed-effects models, use both fixed effects (covariates) and random effects at school and household level.

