The GSFP selected 58 districts in which the programme will be implemented. In each of these districts, two candidate schools were selected and each school was randomly assigned to the treatment or to the control. A protocol was designed in order to ensure that the schools were comparable based on data from the Education Management Information system (EMIS) and that contamination between the two schools in each district will be minimised. This will allow comparison of outcomes of the intervention against the control group at the school level in 58 districts. The 58 schools assigned to the intervention were then randomly assigned to regular GSFP and HGSF+. In this way the randomisation of the HGSF+ intervention occurs at the district level. The number of 58 schools is based on power calculations (see Appendix 1) determined with the objective of achieving statistical validity and representativeness for the main outcomes of interest.

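### The printed impact models omit the matched school pairs and the balancing variables used to allocate, and no estimator is named as primary

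*Protocol article*

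**What the plan says.** **Allocation.** Study area and site selection describes two restrictions on the randomisation. Two matched schools were identified in each of 58 districts, and "The allocation of school feeding and control was then randomised (lottery style) within each pair". Districts were then allocated to HGSF+ or GSFP by "modelling pilot selection using a set of community- and district-level variables and selecting the permutation of allocation that minimises" the R-squared of predicted selection. Random assignment and manipulation of treatments adds that school feeding v control is a school-level comparison ("This will allow comparison of outcomes of the intervention against the control group at the school level in 58 districts"), while HGSF+ v GSFP is compared at district level.

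**Analysis.** Methods of analysis plans impact estimates "using both a ‘difference-in-difference’ (DID) estimator and a single difference analysis of covariance (ANCOVA) model" and names neither as primary. DID is a difference of mean changes between arms. The ANCOVA equation, introduced with "The single difference model specification has the following form", has an intercept, a term that "is a dummy variable for the treatment", the baseline outcome and an error. Standard errors are to be clustered where outcomes are correlated, with school and household as the examples. The robustness check is a multi-level model with covariates and "random effects at school and household level".

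**Other adjustment.** The abstract's conclusion and the Discussion say that variables found to differ at baseline will be controlled for. Neither names the pair or the variables used to choose the permutation.

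**The concern.** The written models do not reflect how allocation was made. If paired schools have similar outcomes, an analysis that ignores the pair counts between-district variation as noise in a within-district comparison. Its standard errors are then larger than the design warrants. Controlling for whatever differs at baseline is not a substitute, because it picks covariates from the observed imbalance and not from the design.

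DID and ANCOVA also give different point estimates whenever the arms differ at baseline, as they do here on several outcomes. The article does not say which estimate is the result. What is at stake is precision that could be had at almost no cost, and a clear answer when the two estimators disagree.

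**Working it through.** **1. Reproduce the planning figures.** Inputs from Appendix 1: Raven's ICC 0.14 with 40 children per cluster; child haemoglobin ICC 0.126 with 20; height-for-age ICC 0.08 with 30. Power is 80% (stated for attendance, assumed for the rest) and allocation is 1:1. A two-sided 5% level is assumed. The unpaired formula for K clusters of size m, in SDs, is

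MDD = (t_0.975 + t_0.80) × sqrt[(4/K) × (ICC + (1−ICC)/m)], df = K−2.

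| Outcome | Computed for 30 / 60 / 120 clusters | Stated |
|---|---|---|
| Raven's (Table 7) | 0.426 / 0.296 / 0.207 | 0.43 / 0.30 / 0.21 |
| Child haemoglobin (Table 9) | 0.437 / 0.303 / 0.212 | 0.44 / 0.31 / 0.21 |
| Height-for-age (Table 10) | 0.353 / 0.245 / 0.172 | 0.35 / 0.25 / 0.17 |

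All agree within 3%. The planned power therefore did not rely on pairing.

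**2. Effect of the pair term, school feeding v control.** With pairing, the variance is multiplied by (1−r), so the ratio of unpaired to paired standard error is 1/sqrt(1−r). The article does not give r; the values below are assumptions. Raven's is the example, with 116 schools. The unpaired MDD is 0.211 SD (df 114). With the pair modelled, df = 116 − 58 − 1 = 57.

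| r | SE ratio | MDD with pair (SD) | Change from 0.211 | True type I error, unpaired test |
|---|---|---|---|---|
| 0 | 1.00 | 0.213 | +1% | 5.0% |
| 0.1 | 1.05 | 0.202 | −4% | 3.9% |
| 0.2 | 1.12 | 0.190 | −10% | 2.8% |
| 0.3 | 1.20 | 0.178 | −16% | 1.9% |

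At the effect for which an unpaired design would have 80% power, the unpaired test on paired data has 81%, 83% and 84% power at r = 0.1, 0.2 and 0.3. Modelling the pair gives 84%, 88% and 92%.

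Here r must be read as the correlation remaining after the baseline outcome is used. DID works on changes and already removes pair effects that are constant over time, so the gain falls mainly to ANCOVA.

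**3. HGSF v GSFP.** There are 29 v 29 districts with one treated school in each. A pair or district effect is confounded with arm in this contrast, so the relevant terms are the variables used to choose the permutation. The article gives neither those variables nor their relation to the outcomes, so the loss cannot be sized.

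**4. Do DID and ANCOVA differ here?** From the two equations, the ANCOVA estimate minus the DID estimate equals (1−β2) × baseline difference. Table 6 means, weighting the three school-feeding arms by n:

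- Literacy: (1661×3.05 + 804×3.58 + 788×3.57)/3253 = 3.31, v 2.75 in control. The difference is 0.56, and 0.56/3.69 = 0.15 SD.
- Digit span: (1664×4.89 + 809×5.13 + 795×4.89)/3268 = 4.95, v 4.56. The difference is 0.39, and 0.39/2.40 = 0.16 SD.

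With β2 of 0.3 to 0.5 (assumed), the estimates differ by 0.5×0.15 to 0.7×0.16, about 0.08 to 0.11 SD. As a yardstick, Table 7 gives 0.21 SD detectable at 120 clusters.

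**5. Which should be primary?** With equal variances and baseline–endline correlation c, Var(DID)/Var(ANCOVA) = 2(1−c)/(1−c²) = 2/(1+c). This is 1.67 at c = 0.2, 1.33 at 0.5 and 1.11 at 0.8. It is never below 1.

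**The case against.** **This belongs to the SAP.** Only a condensed article is shown. Its equation has one treatment dummy for a trial with several arms, so it is schematic, and the text allows further covariates. Pair effects and the ranking of estimators are often settled in a SAP. That is fair as far as it goes. However, the article chose to print the equation and to list the random-effect levels, and what it printed does not match its own allocation. If the SAP has these terms, the remedy is a line of text.

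**Nothing planned is lost.** This stands. A reader might infer that omitting the pairs leaves the trial short of power. The documents do not support that: Tables 7, 9 and 10 reproduce with an unpaired formula, and 58 v 58 schools give 0.211 SD for Raven's against 0.21 in the 120-cluster row. The one comparison whose sample size the Discussion singles out as a particular concern is HGSF+ v HGSF++, which the pair term does not address.

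**The error is on the safe side.** This stands too. With positive r the unpaired test rejects too rarely, so there is no case for excess false positives from this source.

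**The loss could be small.** Correct. A reader might take a raw correlation between paired schools of, say, 0.5 and conclude that standard errors are 41% too large. Both estimators already use the baseline outcome, so only the residual correlation counts, and it is unknown.

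**DID costs ANCOVA nothing.** Also correct: reporting DID alongside does not reduce ANCOVA's precision, and the article itself says ANCOVA is more efficient when autocorrelation is low. What survives is that no estimator is named as the one that decides.

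**Conclusion.** The concern holds in a limited form. The printed models omit the pair and the balancing variables, and two estimators are left unranked. For school feeding v control, the consequence is valid but conservative standard errors, by a factor of 1.05 to 1.20 if the residual within-pair correlation is 0.1 to 0.3. Those values are assumptions. At r = 0, modelling the pair costs about 1% in detectable difference, so the downside is small.

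For HGSF v GSFP the mismatch is real but cannot be quantified from the article.

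The lack of a primary estimator matters in this trial because literacy and digit span differ at baseline by 0.15 to 0.16 SD. If β2 is 0.3 to 0.5, the two estimates differ by about 0.08 to 0.11 SD. Should either significant result be accepted, simulation puts the type I error at 7.9%, 7.4% and 6.5% for c = 0.2, 0.5 and 0.8. The article does not say it would do this; it simply has no rule against it.

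The pairs are schools within a district. The documents do not describe districts as paired with one another, and nothing here should be read that way. This is an improvement the authors should make, not a flaw that invalidates the trial.

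**What to change.** - **Primary estimator.** Name ANCOVA with the baseline outcome as primary and DID as a sensitivity analysis.
- **School feeding v control.** Add pair (district) fixed effects and cluster the errors by pair. Clustering by school once pair effects are in the model would understate the errors, because the residuals of the two schools in a pair mirror each other. Add a pair/district level to the multi-level check for this contrast.
- **HGSF v GSFP.** Adjust for the variables used to choose the permutation, kept to a short list given 58 districts. Use district-level inference and no pair term. Do not add a district level beside school in this contrast: with one treated school per district it cannot be identified.
- **Region.** Optional. Region is described only as a stratifier for sampling districts, not as part of the allocation.

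The cost is wording, as the allocation already produced these variables. Pair effects use 57 degrees of freedom, leaving 57 for the school feeding v control test. The balancing variables use a few more in the other contrast.

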### Markets

Early studies of food prices in Ghana found negligible price differences across the country [18]. Regional equality of consumer prices, however, does not imply the equality of producer prices at a more localised level. The ability of market interventions to influence local price dynamics depends on the level of spatial market integration between local markets. Abdulai [19] analysed the maize market in Ghana and found a high level of integration, meaning a quick transmission of prices from one locality to the other. In these circumstances large purchases of staple food in localised markets are unlikely to produce price changes. Cudjoe et al. tested for market integration for several staple foods in Ghana and found a high level of integration for rice and maize but much less for tubers such as cassava and yam [20]. Prices of the latter items may be strongly localised and transmission between markets may not be easy. It should also be noted that the studies quoted above looked at market integration across large wholesale markets that are well-connected by roads and communication flows. Differences in prices might emerge in more remote and isolated areas even for more commercial crops like maize and rice. We therefore considered studying the impact of the intervention on local market prices, particularly when the food purchased consists of food items that are not highly commercialised such as cassava and yam.

Impact on prices could, in principle, be observed through the household-level questionnaires. The farm gate price could be observed at the household level by including in the questionnaire questions related to prices paid and time of sales. This, however, would complicate the income section of the farmer questionnaire. Consumer prices are more difficult to observe in a standard household survey because the recall time is 7 or 30 days and there is only one survey per year. As part of the programme monitoring activities, price data will be collected, on a monthly basis, for main staple crops in the local market next to each of the selected schools for a sub-sample of farmer households. Collection of prices does not even require visits to markets if stable contacts can be established with collectors in each of the markets and prices could be communicated by phone.

### Heterogeneity of impact

The large dataset will allow for extensive sub-group analysis, including gender, age and geographic characteristics. The impacts of school feeding in different contexts are quite heterogeneous and context-specific [12]. School feeding, for instance, has been associated with marked improvements school participation by girls in rural areas with large gender disparities in access to education [21]. Smallholder farmers targeted by the programme will, in large proportions, be women. From the educational perspective, school feeding impact has also been found to vary with pupil age, as household schooling decisions are also affected by the opportunity costs of education, that tend to increase with age and vary by gender.

The programme is targeted to disadvantaged groups. The main beneficiaries are located in poor, rural districts of the country and the programme has a potential poverty inequality reduction impact at the national level. At the local level, the programme has a potential poverty reduction impact, but the inequality reduction impact will depend on whether:The project will increase enrolment. Children going to school are likely to be from a richer background and from more accessible areasThe project will involve small farmers. The programme might rely on large farmers or traders for the provision of food

### Cost-effectiveness

Cost data will be collected retrospectively following an ingredients approach using a semi-structured questionnaire. The survey will be based on a standardised costing framework capturing capital (fixed) and recurrent costs incurred at the school level. The questionnaire will also cover both cash and in-kind contributions and will be used to estimate both financial and economic costs. Financial costs capture actual expenditures in terms of programme implementation on an annual basis. Economic costs included the opportunity costs of community members, teaching staff and other school-level stakeholders involved in the school feeding and school health and nutrition (SHN) service provision. Opportunity costs of school staff and community members will be calculated using local pay scales. Capital costs will be annuitised over the useful life of all relevant school-level assets using a discount rate of 3 % as per World Bank recommendations. Annuitisation enables an equivalent annual cost to be estimated and reflects the value in-use of capital items, rather than reflecting when the item was purchased [22].

Process and output data covering the adequacy of the service delivery will be collected from monitoring visits on a quarterly basis using standardised data collection forms. Output data will be combined with the costs to provide estimates of cost-efficiency metrics, including costs per beneficiary, kilocalories, iron, and vitamin A delivered. Sensitivity analysis will be undertaken to account for uncertainties in the economic evaluation. The figures obtained in this way will then be compared to figures calculated for other interventions.

Of particular interest is the cost-effectiveness of the community-level component of the intervention. The comparison between the HGSF+ and the regular GSFP groups is roughly equivalent to the comparison between a ‘home-grown’ school feeding project and a standard school feeding project. Many would expect HGSF to be cheaper and more cost-effective because of lower transport costs. However, the alternative procurement source, its distance and affordability is unknown, and hence the difference in costs between the two programmes is an empirical question.

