## Background

School feeding programmes have been a key response to the recent food and economic crises and function to some degree in nearly every country in the world [1]. School feeding is a multi-sectoral intervention with effects across education, health and nutrition, and with the potential for benefits across a life course. Rigorous studies have shown that school feeding programmes can improve school attendance and learning, as well as a child’s physical and psycho-social health (see [2] for a recent review). These effects are heterogeneous and context-specific, depending also on the quality of programme implementation. There is no rigorous evidence on the impact of providing a reliable market for smallholder farmers through ‘home-grown’ school feeding (HGSF) approaches [1, 2]. In HGSF, the demand for food and services from school feeding is channelled explicitly to smallholder farmers and other stakeholders involved in the school feeding supply chain. As most of the studies in the scientific literature in low-income settings involve humanitarian aid, there is also a paucity of evidence on government-led programmes operating at scale in low- and middle-income countries [1]. This study is aimed at addressing these research gaps by evaluating the full cost and impacts of alternative school feeding implementation approaches, across education, health and nutrition, and agriculture domains in Ghana.

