### Random assignment and manipulation of treatments

Households and schools were randomly assigned to three treatment arms:Control group: these are schools and households from communities where the intervention will not be implemented. The intervention will be delayed by at least 3 years in these communities, preferably without informing schools and households. After the 3- year period, these schools will be covered by the GSFP.Regular GSFP group: these are schools and communities where the standard GSFP is implemented, with caterers responsible for the food procurement and preparationHGSF+ group: these are schools and communities where the programme is implemented in addition to a pilot capacity-building component, including training of community-based organisations and other stakeholders, on food procurement, nutrition education, and feedback monitoring. This group will be randomly divided into two sub-groups (HGSF+ and HGSF++) as part of a study focussing on anaemia.

Note that the HGSF+ intervention will be conducted at the district level. Training and monitoring systems involve caterers and exert their effects at the district level, affecting outcomes in schools where the HGSF+ programme is not implemented. On the other hand, the number of districts where the programme is implemented is rather small, which reduces the statistical power of the analysis, and the effects of the school feeding intervention against the control group are best observed at the school level. Hence, we opted for a design that compares the outcomes of the school feeding and control groups at the school level, and that compares outcomes of HGSF+ and regular school feeding (GSFP) at the district level.

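### Costing is specified at school level, so HGSF+ costs that arise above the school are not captured and the incremental cost over GSFP is understated by an unknown amount

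*Protocol article*

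**What the plan says.** The aim, in the Background section of the Protocol article, is stated as "evaluating the full cost and impacts of alternative school feeding implementation approaches". The Cost-effectiveness section then singles out one contrast: "Of particular interest is the cost-effectiveness of the community-level component of the intervention". It equates that contrast with HGSF+ against regular GSFP and leaves the direction of the cost difference open.

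The same section sets the scope of the cost data three times, each time at the school:

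- Framework: "The survey will be based on a standardised costing framework capturing capital (fixed) and recurrent costs incurred at the school level".
- People: "Economic costs included the opportunity costs of community members, teaching staff and other school-level stakeholders".
- Capital: "Capital costs will be annuitised over the useful life of all relevant school-level assets using a discount rate of 3" per cent.

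One sentence names no level: "Financial costs capture actual expenditures in terms of programme implementation on an annual basis".

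On where the added component operates, the section on random assignment says "Note that the HGSF+ intervention will be conducted at the district level", and continues: "Training and monitoring systems involve caterers and exert their effects at the district level". Elsewhere the article describes the pilot as community-level (The HGSF pilot; Cost-effectiveness) and mentions trainings held at school level (Nutrition and health).

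**The concern.** A cost comparison of HGSF+ with GSFP turns on the inputs that one arm has and the other lacks. Here these are training of organisations and caterers, support for agreements between farmers and caterers, monitoring, behaviour-change campaigns and, for HGSF++, fortification. At least the training and monitoring are described as working through the district. A costing framework bounded at the school is poorly placed to see such inputs, and the article names no other source for them.

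The article's Conclusions say that the findings are meant to support policymakers in scaling up the national programme. If part of the HGSF+ input lies outside the cost boundary, HGSF+ will appear cheaper relative to GSFP than it is, on the very question that the article leaves to the data.

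**Working it through.** The article reports no HGSF+ cost, no incremental cost and no cost-effectiveness ratio, so there is no stated figure to reproduce. The check is a reading of the scope followed by simple algebra.

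**1. Does the text reach beyond the school?** The sentence on financial costs could be read more widely, since it names no level. However, the sentence before it says that one questionnaire serves for both financial and economic costs, and that questionnaire rests on the school-level framework. The Survey instruments section lists child, household, school, caterer and community data, with no district, secretariat or pilot-project source. The planned sensitivity analysis is described in general terms and does not mention costs above the school.

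**2. What would be captured?** School-level trainings, the time of community members and school staff, and school assets. The increment is therefore partly covered.

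**3. What is the effect on the contrast?** Write, per child:

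- dC_school = HGSF+ minus GSFP cost at the level the survey covers;
- D = cost specific to HGSF+ above that level, with D ≥ 0;
- dE = HGSF+ minus GSFP effect, taken as positive.

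True incremental cost = dC_school + D. 
Measured incremental cost = dC_school. 
Error = −D, which is never positive. 
The incremental ratio is too low by D/dE.

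District and secretariat costs of the standard programme that are equal in both arms drop out of this difference. They would still be missing from the total cost per beneficiary.

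**4. How large?** Let s be the share of a positive true increment that arises above the covered level. Then measured ratio = (1 − s) × true ratio. The article does not give s, so the values below are assumptions that show only the form of the dependence:

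| Assumed s | Measured ratio as share of true ratio |
|---|---|
| 25% | 75% |
| 50% | 50% |
| 75% | 25% |

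**5. Can the sign change?** The Cost-effectiveness section mentions an expectation of lower transport costs under HGSF. Suppose, purely for illustration, a saving of US$3 per child at school level and D = US$5. The measured difference is −3 and the true one is −3 + 5 = +2, so HGSF+ would be shown as cheaper when it is dearer. This needs a saving smaller than D; the article has no data to say whether that is so.

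**The case against.** The case on the other side has several parts.

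- **The article never says that only school-level costs count, and a condensed article may leave the handling of programme accounts to a fuller plan.** The first half is fair as a matter of wording. But the school-level boundary is stated for the framework, the people and the assets, so this is a stated rule and not silence.
- **Activity data on training and procurement are collected.** The school questionnaire has modules on training and monitoring and on food procurement, and 58 caterers are interviewed. These would help to identify activities, but they are not described as cost records for inputs supplied above the school.
- **The package is largely community-level, and the district remark explains the unit of randomisation.** This stands in part. It rules out the stronger reading that a reader might infer, namely that nearly all of the HGSF+ increment is missed and that its incremental ratio goes to zero. That would follow only if school-level costs were equal in both arms and the whole increment lay above the school. The article supports neither assumption, and it leaves open whether procurement and transport costs differ.
- **Benefits may be under-counted too.** The section on random assignment expects HGSF+ training to affect schools outside the programme, while Table 2 shows one HGSF+ study school in each of 29 districts. This stands. One cannot say that benefits are counted in full, so the net bias in cost-effectiveness is less certain than the bias in cost. It also means that loading a whole district's costs onto one study school would err the other way.
- **It is a secondary economic analysis.** True; no randomised effect estimate is touched.

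**Conclusion.** The point holds in a limited form. The costing boundary as written does not match the stated aim of full cost, nor a contrast whose distinguishing inputs lie partly at district level. Costs specific to HGSF+ above the school drop out, and the measured incremental cost over GSFP is understated.

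The direction for cost follows from D ≥ 0 alone. The size is unknown: the article gives neither HGSF+ costs nor a split by level, and any percentage would rest on an assumed split. The direction for the cost-effectiveness ratio further assumes a positive incremental effect and a comparable count of benefits, which possible effects on other schools in the district make uncertain. The documents do not support a claim that most of the increment is missed.

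This should be corrected before the costing is done, because the contrast affected is the one the article calls of particular interest.

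**What to change.** State in the Cost-effectiveness section that the ingredients costing also covers district and pilot-project costs specific to HGSF+: training, contracting support, monitoring, coordination, and any campaign or fortification inputs supplied centrally. Take them from programme and pilot accounts.

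Allocate these costs over all schools and children that the district activities serve, not only the study schools, and report the number used. Base the HGSF+ versus GSFP comparison on the resulting total and give the school-level figure as a secondary result. For total cost per beneficiary, say whether standard GSFP costs above the school are included, since they cancel only in the contrast between the two feeding arms.

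If these records cannot be obtained, limit the claim to school-level cost-efficiency and withdraw the reference to full cost for this comparison.

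The cost is some extra extraction of records and a rule for allocation. Costing is already retrospective and ingredients-based, so no further survey round is needed. The HGSF+ cost figure may be less favourable as a result.
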